### Blind method

After completing the baseline survey and physical fitness test, the computer random list generated by SPSS 16.0 software was used for randomization. Eligible patients were randomly divided into the experimental group and the control group, with a ratio of 1:1 [16]. The group numbers were enclosed in a carbon-free envelope. The envelopes were kept by the research manager, who was not directly involved in the recruitment or follow-up of any participants, and the group number would then be published. Different people would register as participants and be assigned for intervention, and the results were kept by the research designer until the end of the experiment [17].

### Sample size

The sample size was estimated based on our previous test results [18]. The sample size of this experiment was estimated by the non-inferior test. The non-inferiority margin was 6 and the standard deviation was 10.31. According to the formula, each group should have 44 participants by formulating the inspection level (0.025) and the power of test 1-β (0.2). During baseline inspection and follow-up, 50 participants in each group should participate in the experiment, given a 15% expulsion rate.

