### Implementation

After completing the baseline survey and physical fitness test, the computer random table generated by SPSS16.0 software was used for randomization. The eligible patients were randomly divided into an experimental group and control group, with a ratio of 1:1.

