## Discussion

The effect of qigong intervention on postoperative rehabilitation of breast cancer has been confirmed by randomized controlled trials [9]. However, there are some problems in the traditional outpatient exercise rehabilitation, such as traffic, time consumption, and space occupation, which will affect the patients’ enthusiasm to participate in rehabilitation to a certain extent, and also increases the medical economic burden. The development of Internet technology makes it possible to guide the rehabilitation of remote exercise. Based on this, we designed a randomized controlled trial with a sufficient sample size to verify the rehabilitation effect of remote guidance intervention of qigong on postoperative breast cancer patients and to compare the effects of qigong intervention and traditional exercise rehabilitation.

In addition, most of the study of exercise rehabilitation takes the improvement of patients’ physical fitness level as the main research outcome, which neglects the patient’s subjective feeling and quality of life to some extent. Therefore, the quality of life of breast cancer patients after surgery is set as the first research indicator, followed by the related physical fitness outcomes.

Also, it is not clear whether conventional exercise intervention or qigong intervention can prevent recurrence in breast cancer patients. To answer this question, a follow-up study of larger samples and longer periods of time are necessary. Due to the limitation of research funding, The exercise intervention and follow-up time are relatively short which makes it hard to study the recurrence of tumors in depth. If possible, subsequent studies will look at whether qigong can prevent breast cancer recurrence.

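### The printed inputs need 47 evaluable patients per group, not 44, and 50 randomised with 15% loss leaves about 42, so power is about 76% rather than 80%

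*Protocol article*

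**What the plan says.** All the figures are in the Sample size section of the protocol article. The design is stated as "The sample size of this experiment was estimated by the non-inferior test", and the inputs as "The non-inferiority margin was 6 and the standard deviation was 10.31". The result follows: "each group should have 44 participants by formulating the inspection level (0.025) and the power of test 1-β (0.2"). The allowance for loss is then "50 participants in each group should participate in the experiment, given a 15% expulsion rate". Recruiting methods confirms a total of 100 subjects, and Implementation gives 1:1 allocation.

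The section states no expected true difference, no baseline correlation and no other reduction of variance. It says that the estimate rests on the team's earlier results, which are cited but not reproduced. The Discussion later says that "we designed a randomized controlled trial with a sufficient sample size".

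**The concern.** The paragraph prints both the inputs and the answers, so it can be checked line by line. Three things look wrong: the 44 seems too small for an SD of 10.31, the 50 seems too small for 44 after 15% loss, and the power is given the value of β.

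Both numerical slips run in the same direction. In a non-inferiority trial, lost power means a higher chance that a truly non-inferior intervention fails to show it. Here that chance would be about 24% instead of the intended 20%. A reader who takes the paragraph and the Discussion at face value would believe that the trial is protected at 80% under its own dropout assumption.

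**Working it through.** **Inputs**

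- Margin 6 and SD 10.31 (Sample size).
- Level 0.025 (Sample size). Sidedness is not stated. It is taken as one-sided, which is usual for non-inferiority and matches the 95% confidence intervals in Statistical analysis.
- Power 0.80. The text prints "the power of test 1-β (0.2"), read here as β = 0.2.
- 1:1 allocation (Implementation) and 15% loss (Sample size).
- True difference 0. This is an assumption, the usual default when none is given.

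**Step 1: the evaluable number**

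n per group = 2 × [SD × (z₀.₉₇₅ + z₀.₈₀) / margin]²

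= 2 × [10.31 × (1.960 + 0.842) / 6]² = 46.35, so 47. With the noncentral t distribution it is 48.

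The stated 44 is not reproduced. Other readings with margin 6 and SD 10.31:

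| Reading | n per group |
|---|---|
| One-sided 0.025, power 75% | 41 |
| One-sided 0.025, power 80% | **47** |
| One-sided 0.025, power 85% | 54 |
| One-sided 0.05, power 80% | 37 |
| One-sided 0.05, power 85% | 43 |
| Two-sided 0.025, power 80% | 57 |
| One-sided 0.025, power literally 0.2 | 8 |

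None gives 44. The last row also shows that 0.2 cannot have been used as the power.

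The formula does reach 44 with inputs that the article does not print:

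- SD 10 instead of 10.31: 43.6.
- A true difference of 0.16 in favour of qigong: 46.35 × (6/6.16)² = 43.97.
- A baseline to week-12 correlation of about 0.23: 46.35 × (1 − 0.23²) = 43.9.

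Which of these, if any, lies behind the 44 cannot be told from the document.

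**Step 2: the allowance for loss**

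This step uses only the plan's own 44 and 15%.

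- Correct inflation: 44/0.85 = 51.8, so 52 per group.
- Simple multiplication: 44 × 1.15 = 50.6, so 51 per group.
- Loss that 50 can absorb: 1 − 44/50 = 12%.
- Left after 15% loss: 50 × 0.85 = 42.5, below the stated 44.

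**Step 3: power**

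Power = Φ(6 / [10.31 × √(2/n)] − 1.960)

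| Evaluable per group | Power (z) | Power (t) |
|---|---|---|
| 42 | 76.0% | 75.0% |
| 42.5 | 76.5% | 75.5% |
| 44 | 77.9% | 77.0% |
| 47 | 80.5% | 79.7% |
| 48 | 81.4% | 80.6% |
| 50 (no loss) | 82.9% | 82.2% |

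For n = 42: 10.31 × √(2/42) = 2.250; 6/2.250 = 2.667; 2.667 − 1.960 = 0.707; Φ(0.707) = 0.760.

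**Step 4: the size for 80% under 15% loss**

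47/0.85 = 55.3, so 56 randomised per group, or 112 in total against 100.

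**Step 5: what baseline adjustment could recover**

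If 10.31 is an unadjusted SD, adjustment multiplies the requirement by (1 − ρ²). Setting 46.35 × (1 − ρ²) ≤ 42 gives ρ² ≥ 0.094, so ρ ≥ 0.31.

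**The case against.** The strongest reply is that the 47 depends on a true difference of zero, which the article does not state. The calculation draws on earlier results that are not shown. A very small expected advantage for qigong, or a weak baseline correlation, would give 44, and a condensed article may simply have left that input out. This stands as a limit on the first step: 44 does not follow from what is printed, but an unprinted input could explain it.

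It does not touch the second step. No unseen input makes 50 × 0.85 equal to 44.

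A second reply is that 76% belongs to an unadjusted comparison, while Statistical analysis already plans a mixed model using baseline variables. If 10.31 is an unadjusted SD, 42 per group gives power of about 80% at a correlation of 0.3, 83% at 0.4 and 87% at 0.5. This also stands, so 76% must be labelled as unadjusted. But the Sample size section claims no such gain and does not say what kind of SD 10.31 is. If it already refers to change scores or adjusted scores, the gain shrinks.

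Third, the gap is small, and 1-β = 0.2 is a slip of notation that alters no number. Both are true. With no loss at all, 50 per group would exceed 80%. The slip still needs correcting, and the plan itself expects 15% loss.

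**Conclusion.** The concern holds: the paragraph is wrong as written. From the printed inputs the requirement is 47 evaluable per group (48 by t), not 44. The loss step fails on the plan's own figures, since 50 per group leaves about 42 at 15% loss. Power is then about 76% (75% by t), roughly 4 points below target.

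The 47 and the 76% rest on one-sided 0.025, a true difference of zero, β = 0.2 and no gain from baseline adjustment. The failure of the loss step rests on none of these. The trial is not badly underpowered, and adjustment may close the gap, but the document does not show that it does.

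**What to change.** Rewrite the Sample size paragraph. State that 0.025 is one-sided, that the assumed true difference is zero, and that β = 0.2 with power 1-β = 0.8. If 44 came from an expected difference or a baseline correlation, print that input. Even then, 15% loss requires 52 randomised per group, 104 in total.

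Then choose one of these:

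1. **Keep 100 patients and restate the power.** Give 47 evaluable per group as the requirement for 80%, about 42 per group expected at 15% loss, and unadjusted power of about 76%. Drop or qualify the claim of sufficient size in the Discussion. The cost is a text correction and a slightly less favourable stated power.
2. **Keep 100 patients and state a baseline-adjusted power.** Say whether 10.31 is an unadjusted SD and justify the assumed correlation. About 0.31 or more is needed for 80% with 42 per group. The cost is again text only, provided that the earlier data support the correlation.
3. **Randomise 56 per group, 112 in total.** This restores 80% without relying on adjustment, but it means 12 more patients and is a recruitment change.

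Option 1 or 2 is enough to make the plan consistent.

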## Discussion

The effect of qigong intervention on postoperative rehabilitation of breast cancer has been confirmed by randomized controlled trials [9]. However, there are some problems in the traditional outpatient exercise rehabilitation, such as traffic, time consumption, and space occupation, which will affect the patients’ enthusiasm to participate in rehabilitation to a certain extent, and also increases the medical economic burden. The development of Internet technology makes it possible to guide the rehabilitation of remote exercise. Based on this, we designed a randomized controlled trial with a sufficient sample size to verify the rehabilitation effect of remote guidance intervention of qigong on postoperative breast cancer patients and to compare the effects of qigong intervention and traditional exercise rehabilitation.

In addition, most of the study of exercise rehabilitation takes the improvement of patients’ physical fitness level as the main research outcome, which neglects the patient’s subjective feeling and quality of life to some extent. Therefore, the quality of life of breast cancer patients after surgery is set as the first research indicator, followed by the related physical fitness outcomes.

Also, it is not clear whether conventional exercise intervention or qigong intervention can prevent recurrence in breast cancer patients. To answer this question, a follow-up study of larger samples and longer periods of time are necessary. Due to the limitation of research funding, The exercise intervention and follow-up time are relatively short which makes it hard to study the recurrence of tumors in depth. If possible, subsequent studies will look at whether qigong can prevent breast cancer recurrence.

## Abbreviations

Sf-36: The MOS 36-item Short Form Health Survey
PF: Physiological function
RP: Role physical
BP: Bodily pain
GH: General health
VT: Vitality
SF: Social function
RE: Role emotional
MH: Mental health
